## Abstract

**Background:**

Beyond its classical role in calcium homoeostasis and bone metabolism, vitamin D deficiency has been found to be associated with several diseases, including diabetes, non-alcoholic fatty liver disease, and even obesity itself. Importantly, there are limited data on therapeutic strategies for vitamin D deficiency in bariatric patients, and the procedure-specific guidelines may not be sufficient. To improve long-term outcomes, nutritional screening and appropriate supplementation to prevent nutrient deficiencies are urgently needed. Therefore, the aim of this study is to examine effects and safety of a forced dosing regimen of vitamin D versus conventional dose supplementation on vitamin D levels and other parameters in bariatric patients.

**Methods/Design:**

The study includes loading plus repeat dosing compared with repeated administration of vitamin D without a loading dose, according to guidelines, in a prospective, double-blind, randomized controlled trial. Up to a triple oral loading dose is given on day 1, then 2 and 4 weeks after surgery (100,000 IU dose each time), followed by an oral maintenance dose (3420 IU/day). The control group (*n* = 25) will receive placebo, followed by administration of a standard dose (3420 IU/day). We hypothesize that a significant increase in vitamin D levels will occur in patients in the treatment group (*n* = 25) by 24 weeks after surgery. Further measurements are aimed at evaluating changes in inflammation, bone turnover, insulin resistance, blood pressure, liver, mental health, and gut microbiota of patients undergoing omega-loop gastric bypass surgery. Furthermore, possible associations between concentrations of vitamin D, the involved enzymes, or vitamin D receptor in adipose and/or liver tissues will be determined.

**Discussion:**

To our knowledge, this trial is the first of its kind with this type of vitamin D supplementation in bariatric patients. Its major strength is the design and implementation of evaluation of influencing factors such as liver function, bone health, inflammation, insulin resistance, blood pressure, symptoms of depression, or microbiota. This alternative vitamin D dosing regimen has the potential to be a safe, fast, evidence-based treatment of vitamin D deficiency in bariatric patients. Owing to the increasing number of bariatric patients, it is also of interest to elucidate the link between obesity and vitamin D.

**Trial registration:**

ClinicalTrials.gov identifier: NCT02092376. Registered on 17 March 2014.

## Background

Obesity is a global epidemic [1] that is associated with various comorbidities. It is part of the definition of the metabolic syndrome, including arterial hypertension and disturbances in glucose and lipid metabolism, with an inherent risk of development of cardiovascular disease [2, 3]. These associated issues and obesity itself contribute to increased morbidity, mortality rates, and health care costs [4, 5].

Weight reduction is not easy to achieve and maintain. Consequently, many individuals, especially those with comorbidities, are referred for bariatric weight loss surgery as a way to treat obesity and (pre)diabetes successfully [6]. Bariatric surgery is associated with effective and long-term weight loss in morbidly obese patients and decreases overall mortality [7]. At present, there are three categories of bariatric procedures: (1) purely gastric restriction (e.g., gastric banding); (2) gastric restriction with some malabsorption, as represented by the Roux-en-Y (RYGB) or omega-loop gastric bypass (OLGB), reducing the intake and absorption of food [8]; and (3) gastric restriction with significant intestinal malabsorption (e.g., biliopancreatic diversion) [9]. In general, the more complex the procedure, the better are the results in terms of weight loss [10]. Because of this situation and the fact that obesity itself is often accompanied by nutritional deficiencies, bariatric patients often have perioperative nutrient deficiencies [9, 11–18]. These deficiencies should be detected and clinically addressed early to avoid postoperative complications. To improve long-term outcomes following bariatric surgery, nutritional screening and prescribing appropriate supplementation to prevent nutrient deficiencies is recommended at an early stage in pre- and postoperative care owing to the malabsorption and insufficient intake. Vitamin D deficiency is common following bariatric surgery and has been reported to occur in 50–80 % of bariatric patients [19–22]. There are limited data on how best to treat low vitamin D status in bariatric patients. Procedure-specific guidelines may not be helpful in daily practice, and the updated guidelines have not been evaluated yet [23].

Recent studies have shown that vitamin D may have an impact on the prevention of many diseases, including autoimmune disorders, hypertension, cancers, diabetes [3, 24–26], depression [27–29], and, even more theoretically, probably obesity itself [30].

Obesity is frequently characterized by reduced vitamin D bioavailability, insulin resistance, and a chronic inflammatory response. There is a relationship between serum concentrations of 25-hydroxy-vitamin D (25-OHD) and several circulating inflammatory markers in severely obese individuals [31]. This observed relationship between low vitamin D status and obesity may be caused by mechanisms such as sequestration in adipose tissue. The mechanisms underlying the inverse relationship between obesity and vitamin D deficiency are largely unknown. Low serum 25-OHD might contribute to obesity by affecting lipogenesis and/or adipogenesis in the adipose tissue. Interestingly, recent studies [32] suggest that the adipose tissue could be a direct target of vitamin D and that the hormone may modulate adipose tissue formation and function [33–37].

Obesity has recently been associated with non-alcoholic fatty liver disease (NAFLD). NAFLD comprises a disease spectrum ranging from relatively benign hepatic steatosis to more severe steatohepatitis, fibrosis, cirrhosis, and ultimately liver cancer [38]. It has become the most common form of chronic liver disease in Western countries, with a prevalence approaching 50 % of the population (already 40 % in the European Union) [39, 40]. It is estimated that NAFLD will be the number 1 indication for liver transplants in the United States in 2020 [41]. Currently, surgical treatment of coexisting NAFLD in morbidly obese patients is an evolving matter of debate [42]. A few studies propose that low levels of vitamin D may contribute to the development of NAFLD [43]. However, the mechanisms underlying the association of vitamin D and NAFLD are not yet fully understood. Recent animal studies have shown that vitamin D has an important role in the regulation of oxidative stress, the production of proinflammatory cytokines [44, 45], hepatocyte apoptosis [46], and even liver fibrosis [47]. Furthermore, NAFLD is present in approximately 90 % of bariatric patients [48, 49], and up to 5 % of these patients may have unsuspected cirrhosis [50–52]. Because NAFLD is associated with the presence of obesity, glucose and/or lipid disturbances, and arterial hypertension, it is now considered the hepatic manifestation of the metabolic syndrome.

There are limited data on therapeutic strategies for vitamin D deficiency in bariatric patients, and procedure-specific guidelines may not be very helpful in daily clinical practice. Nevertheless, in the 2013 clinical practice guidelines [23], the American Association of Clinical Endocrinologists, the Obesity Society and American Society for Metabolic and Bariatric Surgery recommend a vitamin D supplementation of at least 3000 IU per day and to titrate to the therapeutic 25-OHD level of >75 nmol/L. This recommendation outlines the best evidence level (grade A) [23], which is based on a single randomized controlled trial done in the United States [53]. In that study, the authors attempted to find the optimal vitamin D treatment dose after surgery. Patients who had undergone RYGB were randomized to three doses of cholecalciferol: 800 IU, 2000 IU, and 5000 IU per day. The authors found that all groups had insufficient vitamin D levels at baseline and after 12 months; sufficient vitamin D concentrations were reached in only 44, 78, and 70 % of the patients in the respective groups [53]. Thus, even with very high-dose supplementation, it may be challenging to achieve normal 25-OHD levels in bariatric patients [54].

Vitamin D has multiple physiological functions beyond its classical role in calcium homoeostasis and bone metabolism, and morbidly obese persons have an increased risk for low circulating 25-OHD levels [55, 56] owing to the storage of vitamin D in adipose tissue [55].

Therefore, randomized controlled trials with vitamin D supplementation, such as the present study (Link between Obesity And Vitamin D in bariatric patients with omega-loop bypass surgery [LOAD]), are needed to establish and further pursue evidence-based and potentially optimal treatment regimens for the increasing number patients with low vitamin D status following bariatric surgery and to define more carefully the impact of specific surgical factors on vitamin D status.

## Methods/Design

### Overview

This prospective, double-blind, randomized controlled intervention trial includes administration of a vitamin D loading dose and repeat doses in patients undergoing bariatric surgery. A stratified randomization design is being used to obtain comparable groups to ensure that baseline variables (25-OHD, age, and sex) are evenly distributed between groups. Subjects are randomly assigned to the intervention or control group. In this study, 50 bariatric patients planning to undergo OLGB will be recruited. Over the first month postoperatively (day 1–3, weeks 2 and 4), they will receive the loading dose of vitamin D. Afterwards, the maintenance dose will be given up to 24 weeks and until the follow-up visit. An overview of the study design and the assessment points is provided in Fig. 1. The study was approved by the local ethics committee of the Medical University of Vienna (reference number 1899/2013) by the Austrian Competent Authority (reference number LCM-718280-0001), and it complies with the Declaration of Helsinki [57]. Furthermore, the protocol was registered at ClinicalTrials.gov (identifier: NCT02092376) and EudraCT (identifier: 2013-003546-16). The study methods are in accordance with the 2010 Consolidated Standards of Reporting Trials (CONSORT) Statement guidelines for reporting randomized trials [58].

**Fig. 1 Fig1:**
[figure not shown]
Study design and assessment points

### Preevaluation

The methods in this study are built upon a cohort study in which investigators evaluated inter alia the vitamin D status of 50 morbidly obese patients who underwent OLGB [54]. The findings of the evaluation illustrated that 96 % had vitamin D deficiency preoperatively and that, after non-standardized vitamin D supplementation, 80 % still had vitamin D deficiency 12 months postoperatively [54]. Additionally, there is evidence that, despite forced vitamin D supplementation, some patients are still at risk for increased bone resorption [22, 59, 60]. It could be possible that morbidly obese patients might need higher 25-OHD levels to reduce the risk for developing metabolic bone disease, osteoporosis [61], or other associated disorders.

### Study objectives

#### Primary outcome measures

The primary objective of the present study is to examine whether administration of up to three oral loading doses in the first month postoperatively (day 1 and at weeks 2 and 4), followed by an oral maintenance dose (intervention group) in bariatric patients can significantly increase 25-OHD levels 24 weeks after surgery as compared with a control group receiving placebo followed by the standard daily maintenance dose (control group).

#### Secondary outcome measures

In further measurements, changes in inflammation, bone turnover, bone mineral density (BMD), insulin resistance, blood pressure, body fat mass, stage of liver stiffness and steatosis, and mental health (improvement of depression) will be investigated. Furthermore, we will assess the adipose depot vitamin D concentrations and expression of enzymes (25-hydroxylases such as CYP27A1, CYP2R1, CYP2J2, CYP3A4, CYP2C11, and CYP27B1, as well as 24-hydroxylase CYP24A1) and vitamin D receptor in subcutaneous tissue (SAT), visceral adipose tissue (VAT), and liver tissue samples collected during surgery. Additionally, the liver tissue samples will be used in addition to the prescribed study-related measures for a histological examination as extended diagnostics for NAFLD or non-alcoholic steatohepatitis and molecular analysis to further evaluate disease specific mechanisms [62, 63].

### Recruitment and eligibility

We are recruiting bariatric patients planning to undergo OLGB and who are in- and/or outpatients in the obesity clinic at the Department of Internal Medicine III or the Department of Surgery at Vienna General Hospital. The inclusion and exclusion criteria are shown in Table 1.

**Table 1 Tab1:** Inclusion and exclusion criteria

Inclusion	Exclusion
Men and women ages 18–100 years	Another planned form of bariatric surgery
Planned OLGB	Hypercalcemia (calcium >2.63 mmol/L) or hypocalcemia (calcium <1.75 mmol/L)
25-OHD <75 nmol/L	Renal insufficiency (creatinine >133 μmol/L or GFR <50 ml/min)
BMI >40 or ≥35 kg/m^2^ with comorbidities	Primary hyperparathyroidism
Body weight <150 kg (owing to limitation of DEXA measurement)	Malignancy
Capability to consent	Infection (e.g., HIV)
	Medical conditions requiring daily calcium supplements or antacid use
	Known hypersensitivity to cholecalciferol
	No capability to consent
	Imprisoned persons

*Abbreviations*: *BMI* body mass index, *DEXA* dual-energy X-ray absorptiometry, *GFR* glomerular filtration rate, *25*-*OHD* 25-hydroxy-vitamin D, *OLGB* omega-loop gastric bypass

**Table 2 Tab2:** Measurements at several time points

	Name	Screening		Intervention								Follow-up
	Duration	12 months		6 months								6 months
Visits	Time		Surgery	Days 1–3	Wk 2	Wk 4	Wk 8	Wk 12	Wk 16	Wk 20	Wk 24	Wk 48
Anamnesis	Anamnesis	X									X	X
	Body weight	X			X	X	X	X	X	X	X	X
	Anthropometry	X				X	X	X	X	X	X	X
	Dietary assessment, BDI	X				X		X			X	X
Bone density	DEXA	X									X	X
Liver and microbiota	FibroScan and CAP^TM^	X				X		X			X	X
	Stool samples	X				X		X			X	X
Biopsies	Liver, SAT, VAT		X									
Supplementation	Loading dose			X	X	X						
	Maintenance dose					X	X	X	X	X	X	X
Blood parameter	Vitamin D	X			X	X	X	X	X	X	X	X
	Biochemical	X			X	X	X	X	X	X	X	X
	Liver	X				X		X			X	X
	Inflammation	X			X	X	X	X	X	X	X	X
	Insulin resistance	X			X	X	X	X	X	X	X	X
	Bone turnover	X				X		X			X	X

*Abbreviations*: *BDI* Beck Depression Inventory, *CAP* controlled attenuation parameter; *DEXA* dual-energy X-ray absorptiometry, *SAT* subcutaneous adipose tissue, *VAT* visceral adipose tissue

### Sample size calculation

The study is powered to detect differences among the groups for 24-week serum 25-OHD levels. On basis of the preevaluation (cohort study), the placebo group was conservatively estimated to have an average 24-week 25-OHD level of 50 ± 30 nmol/L. For sample size calculation, the difference in 25-OHD levels between groups will be considered. Given a clinically relevant difference of 30 nmol/L and a standard deviation of 35 nmol/L of the differences, a two-sided significance level of 0.05, a sample size of 22 per group is needed to reach 80 % statistical power. Because imputation for dropouts of 20 % may have some inestimable effect on the assumed standard deviation of the differences, the sample size is increased to 25 per group. To reach this sample size, a total of 50 bariatric patients in the study are needed. The primary endpoint will be analyzed according to the intention-to-treat principle.

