Finally, one might assume that the rather small sample size of 50 bariatric patients in the proposed study might be underpowered to detect a significant difference between groups. However, the study is powered to detect differences between the groups for 24-week serum 25-OHD levels, with a given clinically relevant difference of 30 nmol/L and a standard deviation of 35 nmol/L of the differences. Thus, if high-dose supplementation with vitamin D is indeed effective, a reduction of vitamin D deficiency after 24 weeks would not be unrealistic.

In conclusion, this vitamin D supplementation regimen has the potential to be a safe, orally available, cheap, and evidence-based treatment of low vitamin D status following bariatric surgery in this increasingly prevalent group, and the study probably also is an opportunity to find an association between obesity and vitamin D deficiency.

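### Raising 22 to 25 per group leaves about 20 observed week-24 values per group at the assumed 20% dropout, so 80% power rests on an imputation effect that the protocol does not quantify

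*Protocol article*

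**What the plan says.** The Sample size calculation section of the protocol article sets out the inputs: "Given a clinically relevant difference of 30 nmol/L and a standard deviation of 35 nmol/L of the differences". With a two-sided 0.05 level, "a sample size of 22 per group is needed to reach 80 % statistical power". The next sentence gives the reason for enrolling more. With 20% of patients expected to drop out, it argues that because imputing their values "may have some inestimable effect on the assumed standard deviation of the differences, the sample size is increased to 25 per group", which makes 50 in total. The section ends by placing the primary endpoint under intention to treat.

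The Discussion returns to the subject. It raises the worry that 50 patients may be too few and answers that "the study is powered to detect differences between the groups for 24-week serum 25-OHD levels", repeating the 30 and 35 nmol/L. Dropout is not mentioned there.

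Two other places matter. The Statistical analysis section includes analysis of covariance with the baseline value as covariate. Table 2 schedules vitamin D blood measurements at screening and at weeks 2, 4, 8, 12, 16, 20, 24 and 48.

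**The concern.** The section gives a base size, a dropout rate and a final size, and they do not fit together on observed data. If one patient in five has no week-24 value, 25 per group yields fewer observed outcomes than the 22 the calculation requires. The protocol relies on imputation to bridge the gap, says that the effect of imputation on the SD cannot be estimated, and then allows three patients per group for it.

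At stake is how a null result would be read. The Discussion uses the powering statement to answer the objection that the trial is small, so a reader would take the type II error as about 20% whatever the dropout. The protocol shows that only for low dropout, or if imputation costs little.

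**Working it through.** **Inputs, all from the Sample size calculation section:** difference 30 nmol/L; SD 35 nmol/L, which reproduces the stated size when used as the common SD in a two-sample comparison; alpha 0.05 two-sided; power 80%; dropout 20%; 25 enrolled per group.

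**1. Reproduce the plan's figure.** Normal formula: n = 2 × (1.960 + 0.842)² × (35/30)² = 21.4, so 22 per group. This matches. The noncentral t distribution gives 79.3% power at 22, so a t test needs 23 (81.1%).

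**2. Observed outcomes at 20% dropout.** 25 × 0.80 = 20 per group.

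**3. Dropout that 25 can absorb.** 1 − 22/25 = 12%. Keeping 22 observed at 20% dropout takes 22/0.80 = 27.5, so 28. Starting from the t-based 23, it is 23/0.80 = 28.75, so 29.

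**4. Unadjusted power by number of fully informative patients.** The noncentrality is (30/35) × √(n/2).

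| n per group | Noncentral t | Normal formula |
|---|---|---|
| 20 | 75.2% | 77.4% |
| 22 | 79.3% | 81.1% |
| 23 | 81.1% | 82.8% |
| 25 | 84.4% | 85.8% |
| 28 | 88.3% | 89.4% |

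Compared within one formula, going from 22 to 20 costs about 4 percentage points.

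**5. How much imputation effect three extra patients cover.** Count all 25 per group as fully informative, hold the difference at 30 and let the SD rise. Power falls to 80% at an SD of 37.1 (t) or 37.9 (normal), a rise of 6% to 8% over 35. If imputation instead shrinks the difference, for example to 27 or 24 nmol/L (assumed values, for range only), t-test power with 25 per group at SD 35 is 76.2% or 66.1%.

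**6. What could be recovered.** The protocol gives no correlation, so these figures are assumptions.
- Baseline adjustment with 20 completers per group: the SD becomes 35 × √(1 − ρ²), with 37 degrees of freedom. Power by t is 76.9% at ρ = 0.2, 79.0% at 0.3 and 82.1% at 0.4. It reaches 80% at ρ of about 0.34 (t) or 0.25 (normal).
- Imputation of missing week-24 values from one predictor observed in everyone, missing at random, with no adjustment otherwise: effective n = 1/[(1 − r²)/20 + r²/25]. Reaching 22 needs r of about 0.67, and reaching 23 needs about 0.81. As r falls to 0, effective n falls to 20.

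**The case against.** The strongest reply is that the protocol never presents 25 as 22 inflated for losses. It says that dropouts are imputed, that imputation may change the SD, and that the three extra patients are a margin for that. Under intention to treat the planned analysis has 25 per group, with nominal power of 84–86%. This is a fair account of the text. A reader might infer from the arithmetic that the plan analyses 20 completers per group and has 75% power; the document does not support that, because 75–77% describes an unadjusted complete-case comparison that it does not propose. What the reply does not establish is that 25 with imputation is worth 25 observed. Imputing the missing values cannot by itself restore the lost information, and the margin covers an SD rise of only 2 to 3 nmol/L against an effect the protocol calls inestimable.

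A second reply is that baseline adjustment and the earlier 25-OHD visits carry real information about dropouts, which a completer t test discards. This stands. A baseline correlation of about a quarter to a third would be enough to restore 80% with 20 completers. But the protocol states no such correlation, and its power statement does not invoke one.

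A third reply is that the choice of imputation method is commonly left to the full protocol or analysis plan, which is not shown. That is right, and its absence from the article is not counted against the trial. For the same reason it cannot be said that imputed values would be analysed as if observed, with standard errors that are too small.

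Finally, recruitment closed in April 2015 according to the Trial status section, so the sample size is fixed and only the wording and the analysis can change.

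**Conclusion.** The point holds in a limited form. At the protocol's own 20% dropout, 25 per group leaves about 20 observed week-24 values per group. The required 22 is preserved only up to 12% dropout. Unadjusted power on observed data is 75.2% (t) or 77.4% (normal), against 79.3% or 81.1% at 22. The 84–86% for 25 analysed is an upper figure that counts every imputed value as a full observation.

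A reader might go further and say that the stated 80% is not delivered, or that a type II error of 25% replaces one of 20%. Neither follows. The first ignores the planned imputation and baseline adjustment, whose gain is unknown and not shown to be zero. The second sets a t-based figure against a target met with the normal formula. The supportable statement is that 80% at 20% dropout is not demonstrated.

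These figures assume a difference of 30 nmol/L, a common SD of 35 nmol/L and equal dropout in the two groups. The shortfall is modest, but the statement should be corrected because the Discussion relies on it.

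**What to change.** Restate the power in the Sample size calculation and in the Discussion along these lines: *Enrolling 25 per group gives about 80% power with up to 12% dropout. At 20% dropout, unadjusted power on observed data is about 75–77%; any recovery depends on baseline adjustment and on earlier 25-OHD values, whose correlation with week 24 is not assumed here.* This costs two sentences and a slightly less favourable power figure. No extra patients are needed.

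Optionally, estimate the week-24 contrast with a baseline-adjusted mixed model for repeated measures on the 25-OHD visits already scheduled at weeks 2, 4, 8, 12, 16, 20 and 24. Dropouts' partial data then contribute, and the standard errors reflect what was observed. The cost is a missing-at-random assumption, which should be stated, and slightly more analysis work.
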